**Methods/design:**

This is a prospective, randomized, double-blind, placebo-controlled, and multicenter trial. The trial will enroll 324 participants with chronic stable angina (Qi Stagnation and Blood Stasis syndrome). All participants will have received the conventional therapy of chronic stable angina. Participants will be randomized into two groups, conventional therapy plus SJP group and conventional therapy plus placebo group. Eligible participants will receive either SJP or placebo (five pills administered orally, three times daily) in addition to conventional treatment for 24 weeks. The primary outcomes are the symptom improvement rate of angina from baseline to 4 weeks after inclusion and major adverse cardiovascular events (MACE). The secondary outcomes are angina classification (CCS), improvement of traditional Chinese medicine (TCM) syndromes, Seattle Angina Scale score, the dosage of emergency drugs and the stopping rate, and electrocardiogram (EKG) efficacy. Adverse events will be monitored throughout the trial.

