### Outcomes

The primary outcome is the effect in angina pectoris, a composite endpoint of cardiovascular events (cardiac death, nonfatal myocardial infarction, revascularization with PCI or coronary artery bypass graft, heart failure, and hospitalization for coronary heart disease). The secondary outcomes are angina classification, improvement of TCM syndromes, Seattle Angina Scale score, the dosage of emergency drugs and the stopping rate, EKG efficacy, and scores of the four TCM diagnostic methods.

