### Follow-up and points of data capture

The points of data capture in the trial are as follows: Intervention period (24 weeks): Baseline, medication for 4 weeks ± 2 days, medication for 12 weeks ± 3 days, medication for 24 weeks ± 5 days for hospital visits, and telephone follow-up for 36 weeks ± 7 days after enrolment.

The corresponding items will be measured according to the time point of data collection. The detailed information is shown in Fig. 2.

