### Sample size

The sample size will be calculated based on a 10% increase in effective treatment after treatment. It was hypothesized that the effective treatment rate for patients receiving standard western medicine treatment is 83% and that for patients receiving both traditional Chinese medicine and western medicine treatment is 93%. The participants will be arranged into the treatment or control group in a ratio of 1:1. According to the one-tailed difference test formula, there should be 162 participants in each group (significance level α is 0.05 and power (1-β) is 0.80 in the one-sided test) and the incomplete rate should be less than 20%. A total of 324 participants will be included.

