### Statistical approach

Efficacy will be determined by the full analysis set (FAS) and per protocol set (PPS), while the safety assessment will be based on the safety set (SS). The statistical evaluation of FAS will follow the principle of intention to treat (ITT). For the missing values of the main efficacy evaluation indicators, the method of the last observation carried forward (LOCF) will be used. Continuous variables were shown as mean ± standard deviation (SD) and were compared using the *t* test or the nonpara-metric Mann-Whitney *U* test, as appropriate. The count variables were shown as the number of cases and percentage, and the chi-square test was used for comparative analysis. The symptom improvement rate of angina is to calculate the total score of angina pectoris according to the degree of pain, the number of attacks, and the duration. The total score is effective when it is lower than or equal to 30% of the baseline, and invalid when it is less than 30%. The symptom improvement rate of angina was analyzed by chi-square test. The participants who had any cardiovascular event during 24 weeks of treatment will be identified as the occurrence of cardiovascular events. The RR and 95% confidence interval of the two groups were calculated by logistic regression model. Statistical analysis will be performed using SAS 9.4 software.

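### Carrying the last observation forward to a yes/no MACE outcome scores participants lost without an event as event-free to week 24

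*Protocol article*

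**What the plan says.** The abstract of the protocol article names MACE as one of two primary outcomes, and the Discussion also counts it in the main therapeutic index. The Outcomes section defines it as a composite of cardiac death, nonfatal infarction, revascularization, heart failure and admission for coronary disease.

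The Statistical approach section fixes three things that bear on this point:

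- **Definition:** "The participants who had any cardiovascular event during 24 weeks of treatment will be identified as the occurrence of cardiovascular events".
- **Model:** "The RR and 95% confidence interval of the two groups were calculated by logistic regression model".
- **Missing values:** "For the missing values of the main efficacy evaluation indicators, the method of the last observation carried forward (LOCF) will be used".

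It also says that the full analysis set follows the intention-to-treat principle. The section names no censoring rule and no time-to-event method.

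Two other sections are relevant. Sample size states that "the incomplete rate should be less than 20" per cent. Follow-up and points of data capture lists hospital visits at weeks 4, 12 and 24, and "telephone follow-up for 36 weeks ± 7 days after enrolment".

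**The concern.** LOCF is a questionable but workable device for a symptom score, where the last value says something about the missing one. For a first event it amounts to assuming zero risk after last contact. Someone lost at week 6 without an event has a last observation of no event. That value is carried to week 24, and the person stays in the denominator with 18 weeks of unobserved time counted as event-free.

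Two consequences follow. The 24-week risk is understated in each arm. If one arm loses more participants from MACE follow-up, or loses them earlier, its risk is understated more and it looks better for that reason alone. MACE needs 24 weeks of observation, so it is more exposed to loss than the 4-week symptom outcome.

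**Working it through.** **The plan's own figure.** The article gives no MACE rate, effect or event count. Its only calculation is for the symptom outcome: 83% against 93%, one-sided 0.05, power 0.80. The pooled formula gives

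n = [1.645·√(2·0.88·0.12) + 0.842·√(0.83·0.17 + 0.93·0.07)]² / 0.10² ≈ 129.5, so 130 per arm.

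130 / 0.80 = 162.5, against 162 stated. The figure reproduces and suggests that 20% loss was built in, but it says nothing about MACE. The sizes below are therefore illustrations.

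**Assumptions (not in the documents).** A constant hazard; a true 24-week risk p of 10% in both arms; a fraction d lost, with times of loss uniform over 24 weeks; those lost scored event-free after leaving.

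**Formula.** With λ = −ln(1 − p) on a time scale of 24 weeks = 1, the mean risk observed before leaving is 1 − p/λ. The observed risk is

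(1 − d)·p + d·(1 − p/λ).

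**Numbers.** λ = −ln 0.9 = 0.10536, so 1 − 0.1/0.10536 = 0.0509.

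| Loss d | Observed risk |
|---|---|
| 5% | 0.95·0.10 + 0.05·0.0509 = 0.0975 |
| 10% | 0.90·0.10 + 0.10·0.0509 = 0.0951 |
| 20% | 0.80·0.10 + 0.20·0.0509 = 0.0902 |

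At 20% loss the relative understatement is (0.10 − 0.0902)/0.10 ≈ 10%.

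**Comparison between arms, no true effect.**

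| Loss SJP / placebo | Uniform loss | All loss at week 4 |
|---|---|---|
| 20% / 20% | 1.00 | 1.00 |
| 20% / 10% | 0.0902/0.0951 = 0.95 | 0.91 |
| 20% / 5% | 0.0902/0.0975 = 0.92 | 0.87 |
| 5% / 20% | 1.08 | not run |

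The ratios hardly move when the assumed risk is 5% or 20% instead of 10% (0.948 and 0.949 for 20% against 10%, uniform). With a true ratio of 0.60 (6% against 10%), equal 20% loss leaves 0.0541/0.0902 = 0.60.

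**Bias against random error.** With 162 per arm and 20% against 10% loss, expected events are 162·0.0902 = 14.6 and 162·0.0951 = 15.4. The standard error of the log risk ratio is √(1/14.6 − 1/162 + 1/15.4 − 1/162) ≈ 0.35. The bias, |ln 0.948| = 0.053, is about 0.15 of that.

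**Do event times add power at week 24?** Hardly. At 10% control risk, hazard ratio 0.6, no loss and two-sided 0.05, power is 0.256 by log-rank and 0.248 by comparing proportions. The gain from a time-to-event analysis is the handling of incomplete follow-up.

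**Week 36, if MACE is collected then.** Under the same assumptions, expected events rise from 26 to 38 and log-rank power from 0.256 to 0.353.

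**The case against.** A yes/no outcome over a fixed window that matches the treatment period is a standard and legitimate choice, and at week 24 event times buy almost no power. Both points stand. The fault lies in applying LOCF to that outcome, not in the window.

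The effect is small, and nothing in the article suggests that loss will differ by arm in a double-blind trial. This also stands: the bias shown is a fraction of the standard error and would rarely change a conclusion.

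It can be said that a missing-data rule for MACE belongs in a fuller document that is not shown. That would answer a complaint of silence, but the article states a rule. The LOCF sentence does not name MACE; that it covers MACE follows from MACE being a primary outcome.

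Two stronger readings are tempting:

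- **That up to 20% will be lost for MACE.** The under-20% figure is a ceiling for incompleteness, attached to the symptom sample size. It may include missed visits or stopped study medication, and under intention to treat such participants can still be followed for events. It does not establish how much MACE information will be lost.
- **That the week-36 follow-up is thrown away.** What that call records is in Fig. 2, which is not shown. The text says only that the MACE definition stops at 24 weeks. The general remark on long-term prognosis in the Discussion does not commit the trial to a 36-week outcome.

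**Conclusion.** The point holds in a limited form. As written, the definition and the LOCF rule together score participants lost without an event as event-free to week 24. Under an assumed 10% risk and 20% uniform loss, this lowers the observed risk by about 10% in relative terms in each arm. With no true effect, it moves the risk ratio to about 0.95 when loss is 20% against 10%, and further if loss is early or more unequal. With equal loss the ratio is almost unbiased. The event rate and the difference in loss are assumptions. The documents do not support a claim that the comparison is seriously biased or that collected week-36 MACE data are discarded. The change is still worth making, because MACE is a primary outcome and the bias can be avoided cheaply.

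**What to change.** In the Statistical approach section:

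1. Exclude MACE from the LOCF rule.
2. Define the outcome as time to first MACE within 24 weeks, censored at the last contact with known event status.
3. Report Kaplan-Meier 24-week risks by arm and their difference with a 95% CI, a log-rank test, and a Cox hazard ratio with 95% CI.
4. Treat non-cardiac death, which is not in the composite, as a competing event. If any occur, take the 24-week risks from the cumulative incidence function and read the Cox result as a cause-specific hazard ratio. If none occur, the two risk estimates coincide.
5. Do not stratify by centre: about 30 events over 11 hospitals, at the assumed 10% risk, would leave very sparse strata.
6. If the week-36 call collects MACE, add a supportive analysis to week 36.

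The cost is analysis-plan wording, to be settled before the codes are broken. It needs dates of events and of last contact; the article does not say that both are recorded, so this should be confirmed. The small downside is that censoring must be assumed non-informative. Reporting the number and timing of losses by arm lets readers judge that assumption.

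### The risk ratio for cardiovascular events is assigned to a logistic model, which yields an odds ratio, and no step from one to the other is described

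*Protocol article*

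**What the plan says.** The Abstract names two primary outcomes: the symptom improvement rate of angina and major adverse cardiovascular events (MACE). The Outcomes section describes the second as "a composite endpoint of cardiovascular events (cardiac death, nonfatal myocardial infarction, revascularization with PCI or coronary artery bypass graft, heart failure, and hospitalization", where the hospitalisation meant is for coronary heart disease. The Discussion also treats this composite as a main efficacy measure alongside the effect on angina.

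The Statistical approach section turns the composite into a yes/no variable: "The participants who had any cardiovascular event during 24 weeks of treatment will be identified as the occurrence of cardiovascular events". The next sentence gives the effect measure and the model: "The RR and 95% confidence interval of the two groups were calculated by logistic regression model". By its position it governs the composite. The other primary outcome has its own method, stated just before: "The symptom improvement rate of angina was analyzed by chi-square test".

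The section does not mention an odds ratio, a log link, a Poisson model, standardisation of predicted risks or model covariates. The software named is SAS 9.4.

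**The concern.** A logistic model works on the log-odds scale, so exponentiating its treatment coefficient gives an odds ratio. The article pairs that model with a risk ratio and does not say how one leads to the other. An analyst who follows the sentence literally would most naturally exponentiate the coefficient and print it under the label RR.

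The estimate for a primary outcome would then carry the wrong name. Whenever the arms differ, it would also overstate the relative effect, in whichever direction the effect runs. A later meta-analysis would pool it as the wrong measure.

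This is not a detail merely left to an analysis plan that is not shown. The article states a measure and a model that do not fit together, and an analysis plan that copied the sentence would inherit the problem.

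**Working it through.** **Is there a figure in the plan to reproduce?** Not for this outcome: the article states no MACE rate, RR or OR. Its one design calculation is the sample size, which uses only the effective treatment rates (83% and 93%, one-sided α 0.05, power 0.80, up to 20% incomplete). That calculation gives 130 evaluable per group, and 130/0.80 = 162.5, against 162 stated. It reproduces closely, but it says nothing about MACE.

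**Inputs.** The outcome is binary and the model logistic (Statistical approach). The control risk p0 and the true RR are my assumptions. I take a model with treatment as the only term, since no covariates are named.

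**Formula.** With p1 = RR × p0,

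OR = [p1/(1 − p1)] / [p0/(1 − p0)] = RR × (1 − p0)/(1 − p1).

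If RR < 1 then p1 < p0, the last factor is below 1, and OR < RR. If RR > 1 the inequality reverses. If RR = 1 the two are equal.

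**Example.** For p0 = 10% and RR = 0.70, p1 = 7% and OR = (0.07/0.93)/(0.10/0.90) = 0.0753/0.1111 = 0.677.

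| Assumed control risk | OR if true RR = 0.70 | Overstated reduction, points | OR if true RR = 0.50 | Overstated reduction, points |
|---|---|---|---|---|
| 2% | 0.696 | 0.4 | 0.495 | 0.5 |
| 5% | 0.689 | 1.1 | 0.487 | 1.3 |
| 10% | 0.677 | 2.3 | 0.474 | 2.6 |
| 20% | 0.651 | 4.9 | 0.444 | 5.6 |

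The overstatement is 100 × (RR − OR), in percentage points of relative reduction.

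**Against the trial's precision.** With 162 per arm and assumed event counts, using Wald intervals on the log scale:

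- 8 control against 4 treated events (about 5% control risk): RR 0.50 (95% CI 0.15 to 1.63); OR = (4 × 154)/(8 × 158) = 0.49 (0.14 to 1.65).
- 16 against 8 (about 10%): RR 0.50 (0.22 to 1.14); OR = (8 × 146)/(16 × 154) = 0.47 (0.20 to 1.14).

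In both cases the two measures lead to the same conclusion on significance.

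**The case against.** The strongest reply is that the sentence can be read in a way that makes it correct. A risk ratio can be obtained from a logistic model by standardising its predicted risks, and a condensed article may leave that step to the full protocol or analysis plan. A reader might infer from the text that an odds ratio will certainly be published as a risk ratio and the effect overstated. The documents do not support that: nothing says the raw coefficient will be reported. Mislabelling is the likely result of the sentence, not a certain one. What remains is that measure and model do not match as written.

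A second reply is that the numerical harm may be slight. Participants have stable angina of CCS grade I to III, recent infarction and revascularisation are excluded, and the window is 24 weeks, so a control risk of 5% or less is plausible. This largely stands. It cannot be taken as settled, because the composite includes hospitalisation for coronary heart disease and entry requires at least two angina episodes a week. The article offers no rare-event argument.

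A reader might also apply the mismatch to the effective rates in the Sample size section. There the gap is dramatic: RR = 0.93/0.83 = 1.12, against OR = (0.93/0.07)/(0.83/0.17) = 2.72. The article assigns that outcome to the chi-square test, so this contrast is not an error the plan would produce.

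**Conclusion.** The point holds as an inconsistency of effect measure and label for a primary outcome. If the logistic coefficient is reported as an RR, the relative reduction is overstated by about 0.4 to 1.3 points at control risks of 2% to 5%, 2.3 to 2.6 points at 10%, and 4.9 to 5.6 points at 20%. These figures rest on assumed control risks and on true RRs of 0.70 and 0.50; the article supplies neither.

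The design, the data collected and the symptom improvement analysis are untouched, and the significance test for MACE is little affected. It should be fixed, but it does not threaten the trial's validity.

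**What to change.** Before unblinding, amend the sentence in one of two ways:

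- Keep the logistic model and call its result an odds ratio with 95% CI.
- Keep the risk ratio and name a method that estimates it: log-binomial regression, modified Poisson regression with robust variance, or marginal standardisation from the logistic model with a delta-method or bootstrap interval. All are feasible in SAS 9.4.

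If the risk ratio is kept, possible wording is: *The risk ratio for any cardiovascular event within 24 weeks, with its 95% CI, will be estimated by modified Poisson regression with robust variance.* Adding the risk difference is optional.

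Settling this while the codes are closed keeps the choice of measure independent of the results. The cost is one sentence, one SAS procedure and a minor amendment, which the Data management and quality control section sends to the ethics committee for re-approval. No new data and no change in sample size are needed.

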### Data management and quality control

Any amendments or changes of protocol will be reapproved by the formal process of the ethics committee of Shuguang Hospital. Data management and statistical analysis will be performed by the statistical department in China Evidence-based Medicine Center, West China Hospital, Sichuan University. Independent clinical research associate (CRA) will regularly audit and monitor the study at each hospital. Well-trained researchers will collect and record the study data in the case report form (CRF). To ensure confidence in the data, study-related files including consent forms, the CRF, questionnaires, medical records, and other records will be stored in a locked space or on a password-protected computer in each hospital for 3 years after study completion. Data monitoring will be conducted by the data and safety monitoring committee. Auditing can be conducted to this trial by the quality assurance team at the supporting institution, independent from the investigators.

### Safety assessment

A safety analysis set will be used to summarize and analyze all safety endpoints. Safety assessment will be based on vital signs, laboratory examinations, and adverse events. Vital signs will include the respiratory rate, blood pressure, and heart rate. Laboratory measurements will include a routine blood and urine test, hepatorenal assessment, and electrocardiogram (detailed monitoring schedule is shown in Fig. 2). Adverse events, especially severe adverse events, will be reported to the research group committee within 24 h. The study design refers to Fig. 1. Based on the improvement of symptoms at 24 weeks, post-trial participants will be recommended to have a regular follow-up at the outpatient department.

## Discussion

Myocardial ischemia and hypoxia are critical pathophysiological changes in CHD. Although the treatment of angina pectoris is performed in accordance with the guidelines, many participants do not receive conventional treatments due to side effects, contraindications, and drug-drug interactions. Some participants receive conventional treatment; however, angina symptoms persist. CHD is called “chest pain,” “heartache,” and “true heartache” in the TCM concept [18]. The etiology and pathogenesis of TCM of CAD are deficient in origin and excess in superficiality. One of the main syndrome types is Qi stagnation and blood stasis syndrome. TCM has been used to treat diseases for thousands of years. Many classic formulas have been used in clinical practice. Recently, people are increasingly concerned about the benefits of TCM and potential drug interactions with Western medications, especially for participants with stable angina [15]. The combination of SJP and Western medicine is one conventional approach in the treatment of angina pectoris. Many experimental studies and clinical trials have proved the efficacy in the improvement of cardiocerebral vascular conditions [20–22]. The pathophysiology of SJP in the treatment of myocardial ischemia has not been fully elucidated. The main mechanisms include oxidative stress, calcium overload, the opening of mitochondrial permeability transition pore, and inflammation stimulation. The combination of Ligustrazine and Borneol (the main ingredients of SJP) showed a notable synergistic calcium antagonistic activity, exerting a better vasodilatation function than using any component alone [11]. Thus, it plays a protective role in myocardial ischemia.

Several clinical studies on SJP have confirmed its efficacy in mitigating the symptoms of angina without any serious side effects. A systematic review including 41 trials involving 6276 participants was included in the analysis. A meta-analysis of the clinical efficacy of the results. The analysis showed that SJP can effectively reduce the lipid profile and improve the hemorheology index in patients with CHD. This is due to the effects of its ingredients (borneol and L. chuanxiong), which may improve coronary artery circulation and ECG results. Based on the Jadad score, most of the clinical studies included in the meta-analysis were of poor quality. Only a few studies reported a detailed research methodology [13]. Therefore, it is necessary to scientifically design high-quality, large-scale, clinically proven therapeutic effects of fast-acting Jiuxin pills on angina. Evaluation of the therapeutic effect on cardiovascular disease includes improvement of clinical symptoms and long-term prognosis of the disease. Therefore, in addition to the efficacy in angina pectoris, the main therapeutic index of this experiment also observed the composite endpoint of cardiovascular events (MACE). The medical model has currently changed to the “biological-psycho-social” model [23]; people are no longer satisfied with simple life extension, but they have a higher hope for the quality of life. Therefore, the secondary efficacy in our study design, the indicators, mainly observe the improvement of patients’ symptoms and quality of life, including the secondary outcomes, such as angina classification (CCS), TCM syndromes, and Seattle Angina Scale score (SAQ) [24].

Our clinical design plan is based on the principles of international clinical trials. Strict quality control measures are designed using double-blind, randomized, placebo-controlled, multi-center research methods. A professional independent statistical group is responsible for statistical analysis and reporting, and it will analyze the combined data from all research centers. Strict trial design and supervision during the trial implementation process will ensure a scientific and objective evaluation of the efficacy and safety of SJP in the treatment of angina pectoris.

